## Methods/Design

The study conforms to the guidelines contained in the CONSORT statement for cluster randomised controlled trials [50]. Individual GPs (cluster) will be the unit of randomisation. The study includes one GP only per practice to circumvent the threat of contamination due to cross-over effects. Interventions and analyses will target two levels - the cluster (GP) level and individual (woman) level. The trial will include 40 GPs and consist of two arms - intervention and comparison. Figure 1 presents the anticipated flow of clusters and individual patients over the course of the trial. The study has received ethics approval from the Human Research Ethics Committee of The University of Melbourne.

**Figure 1 F1:**
[figure not shown]
**Flow of participants through trial**.

### Inclusion and exclusion criteria

#### General practitioners

GPs will be eligible if they work three or more sessions per week and are based at a computerised practice. GPs will be excluded if 30% or more of their patients are non-English speaking or if the GP has not been actively practising in the last 12 months.

#### Women

Women will be eligible for the initial screening component of the study if they have consulted the participating GP within the last 12 months and are aged between 16 and 50 years. Women will be excluded if, in exercising clinical judgement, the GP anticipates they may encounter difficulties in providing informed consent, understanding the content of surveys and/or participating in other aspects of the study due to mental or physical health issues, cognitive impairment, intellectual disability or poor English language skills. Additional criteria are required for inclusion in the trial - women will be invited to participate (over the telephone) if they indicate in the screening survey that they have been afraid of their partner or ex-partner in the last 12 months and are interested in hearing more about the **weave **project. Women will be excluded at this stage if it is established during the recruitment phone call that they no longer attend the GP or they are a false-positive. False positives are women who misinterpreted the fear item in that they have never felt afraid of a partner or they have not felt afraid in the previous 12 months.

### Number of participants required

The final sample size of 89 women in each of the two groups will have at least 80% power (alpha 5%, 2-sided test) allowing for a clustering effect (intra-cluster correlation of 0.02 [8]) to detect clinically important differences on the primary outcomes at 12 months between the intervention and comparison groups (See Table 1). To have sufficient power to test our hypotheses, 40 practitioners (20 in each arm) are required in order to allow screening of approximately 500 women per practice (20000 women in total). Based on women's response rates from the **weave **pilot study and *diamond *study [51] 40% of women will return the screening survey (8000). Of these, it is estimated that 10% (800) will have experienced abuse that includes combined physical, sexual and/or emotional abuse in the last 12 months and will therefore screen positive to having been afraid of a partner or ex-partner during this period. Of these, 60% (480) will indicate an interest in hearing more about the project and being contacted by the research team. It is estimated that 70% (336) of these women will agree over the phone to being involved in the trial (a proportion will decline and a proportion will prove ineligible at this stage), 80% (268) of whom will return their baseline surveys and enter the trial. Following randomisation, approximately a third (88) will be lost to follow-up at 12 months based on data from the *diamond *cohort [51] and MOSAIC [52] leaving 89 women per group at 12 months.

**Table 1 T1:** Primary outcomes, measures and hypothesised differences between study groups

Outcome	Measure/tool	Hypothesis
Quality of life	World Health Organisation Quality of Life-Bref [58]	There will be a difference of half of a standard deviation between the two groups (assuming a SD of 20) [66]
Mental health status	SF-12 Mental Component Summary [59]	There will be a difference of half of a standard deviation (SD = 11) between the two groups [67]

Safety planning	Safety plan in the last 12 months	Have a safety plan at 12 months: 10% vs 40%
Safety behaviours	Safety-Promoting Behaviour Checklist [60]	There will be a difference of half of a standard deviation (SD= 2.5) between the two groups [68]

### Recruitment

Multiple strategies will be used to recruit GPs. These include mailing to randomly selected GPs (750 urban, 250 rural; within 150 km radius of Melbourne) registered with the Australasian Medical Publishing Company. GPs will be sent a letter of invitation, information about the project and a faxback form in the mail. If we still require more GPs, we will re-contact eligible practices from this original list, and request that the practice manager advertise the project among GPs with interest in women's health, domestic violence, mental health or research. Additionally, we will mail out to 600 GPs involved in shared maternity care in Melbourne using the same protocol.

Although we will utilise the lists described above as much as possible to minimise selection bias, we will enlist the services of VicReN if required. This is a Victorian-based general practice research network service based at the Primary Care Research Unit at The University of Melbourne. Staff from VicReN will assist by advertising the project in newsletters of the Royal Australian College of General Practitioners (RACGP) and Divisions of General Practice and by engaging GPs using various strategies. All eligible GPs will be asked to read and sign a Memorandum of Understanding and consent form, complete a baseline survey (allowing comparison with the Australian GP population) and to complete the basic education kit. Practices are reimbursed at a rate of $500 for time involved in generating patient lists and GPs will be eligible for RACGP Quality Assurance and Continuing Professional Development points.

### Patient recruitment

Patient recruitment will be done through methods validated in a recent primary care cohort study that screened for probable depression via postal survey, and included a screen for abuse [51]. In **weave**, for each participating GP, a list of female patients, aged 16 to 50 years who consulted the GP at least once in the previous 12 months will be randomly generated (maximum 600 patients per list). The GP will review the list and exclude those women who meet exclusion criteria. The remaining women will be mailed the screening questionnaire together with a letter from their GP endorsing the project, an information sheet, a resource card listing contact numbers for various support agencies and a reply paid envelope. In the survey the respondents are told that the **weave **team is trying to work out ways to improve the care women receive in general practice, and particularly in relation to emotional well-being. At the end of the screening survey, respondents are asked if they would like to hear more about **weave**, the next stage of which involves "completing a survey about relationship and emotional issues (e.g. depression, domestic violence, stress or worry)." A reminder is mailed out from the practice to all women 14 days following mail-out of the screening survey.

Eligible women will be phoned by a research assistant who will explain the nature of the study (a project looking at ways of improving the care women receive from their GP when they are experiencing relationship and emotional issues, such as being afraid of your partner or ex-partner). It will be explained that the project will involve three surveys over approximately 18 months and that they may or may not be invited to see the GP to discuss relationship and emotional issues depending on the group in which they are placed by chance. Those eligible and agreeing to be involved are sent a baseline survey, information sheet, resource card and a reply paid envelope. Once the baseline survey and consent form have been returned, women are officially enrolled in the trial. A reminder is sent to patients 10 days post baseline survey and a phone call reminder at 20 days. All GPs (and their female patients) in a given wave (there will be four waves) are randomised to intervention or comparison once the cut-off for the return of the baseline survey (30 days following mail-out) for the final GP in the wave has been reached.

### Sequence generation and allocation concealment

Allocation to intervention or comparison will be based on clusters rather than individuals. The trial will be run in four consecutive overlapping waves. Approximately 10 GPs will be randomised in each wave. Characteristics of GPs, including age, sex, years of general practice experience and knowledge about management of partner abuse, will be measured at baseline to check the extent to which randomisation creates equivalence across the two groups. To promote comparability of the intervention and comparison clusters with respect to cluster characteristics, practitioners will be stratified according to whether they are urban or rural and block randomisation with random block sizes will be used within each stratum. The randomisation will be performed by a statistician not directly involved in the study and who is blinded to the identity of the practitioners. Allocation of clusters to intervention or comparison will done following collection of baseline data. In other words, at the time of screening and recruitment of women, the allocation of GPs (and therefore, of women) will be unknown.

### Blinding

**weave **is a pragmatic intervention study. Due to the nature of the intervention (professional training plus patient counselling) it is not possible to blind the GPs to their status as intervention or control. Similarly, the immediate project team is not blind to GP participant status as much interaction between the team and the GPs must occur as part of the training and organising for women to attend their counselling appointments. In the same vein, women are not blinded in that they need to be aware that they may (intervention group) or may not (comparison group) be invited by the GP to discuss relationship issues as part of **weave**. Women will be made aware that they will receive surveys regardless of the group they have been assigned to. There is no blinding as regards data collection based on the CONSORT guidelines [50], as the women and GPs themselves complete the surveys (i.e. data were not collected by a research assistant blinded to the allocation). However the wider investigator team (and the statistician) remain blinded to the identity and allocation of GP participants and women.

### Intervention

The **weave **intervention [37] is a multifaceted, practice-based program refined by the multidisciplinary team and project reference group. It consists of professional, patient and organisational elements. The aim of the professional intervention (**weave **Healthy Relationships Training) is to train GPs in how to respond to IPA when women are identified, and to facilitate GPs to deliver a brief counselling intervention to patients who have been afraid of their partner or ex-partner. It will equip practitioners with an innovative, time-efficient and structured approach to use with patients. The intervention was developed with particular attention to overcome the challenges of changing physician behaviour [53] by being practice-based and including group discussion via teleconference, clinical audits, distance learning, evidence-based guidelines [36] and two interactive practice visits [37]. Key elements of the visits are active listening exercises [54], attitudinal exercises [55], involvement of simulated patients and role play of different readiness for change scenarios [40], use of survivors' voices [56], and modelling of non-abusive behaviours in teaching interactions with health providers [55]. As required, additional practice visits, email and telephone support will be provided.

The patient component of the **weave **intervention involves a brief counselling intervention for delivery by the intervention (trained) group GPs within the primary care setting. Female patients who have been 'afraid' of a partner or ex-partner in the last 12 months (participants in the study) will receive a letter from their GP inviting them to make an appointment to discuss relationship and emotional issues. Women will be offered several 30-minute counselling sessions by their GP for relationship issues and their emotional wellbeing. Where women have not made an appointment within a fortnight of receiving the invitation the research assistant will contact them and offer to connect them immediately with the practice to book an appointment. The main aim of the **weave **brief intervention is to assist women to:

• feel listened to, validated and supported by their GP;

• experience increased awareness about the abuse;

• increase their readiness for change and self-efficacy, and;

• increase their safety planning and behaviours.

At the first visit, the GP establishes with the woman the number of sessions that might be required (up to 6). The woman's readiness for change is established and the GP then selects motivational interviewing and/or problem-solving techniques as part of an appropriate response to the woman's position. GPs complete encounter forms during the women's visits to allow gathering of process data on the content of the counselling.

The minimal organisational change component of the intervention involves circulating information about **weave **to the administrative and clinical staff, placing posters on the wall and working with the practice staff to identify suitable and consistent methods of reminder and recall for the women. Each aspect of the organisational change will prioritise the confidentiality of women and will be practice-centred (i.e. guided by advice of the participating GP and practice manager). At the conclusion of the trial, comparison group GPs will be invited to participate in a day long workshop based on the **weave **Healthy Relationships Training Program.

### Data collection

#### Outcome evaluation

Data will be collected from women by postal questionnaire at the screening stage and at three further points over the duration of the project. Similar to other studies in this area [30,31], we will collect data from women in both groups at baseline, and at 6 and 12 months following the invitation to the intervention group women to attend counselling. Development of study materials has been informed by a primary care cohort study on depression which also gathered data on abuse [51].

#### Screening phase

The primary purpose of the screening questionnaire is to identify women who have been afraid of a partner or ex-partner in the last 12 months and of those, the women willing to be contacted by the project team. The additional items in the survey ask about depression, smoking, alcohol, anxiety, dietary issues and exercise. These help to conceal the purpose of the survey and protect participants. Responses are on a five point likert scale ranging from 'None of the time' to 'All of the time'. If a woman selects an option other than 'None of the time' for the afraid question, and indicates an interest in hearing more about the project, then she is contacted and invited to participate in the trial. Other items include a sub-dimension of the General Practice Assessment Questionnaire [57] and sociodemographic items. We also included items to establish whether women have disclosed being afraid to a GP previously, if they would use help from the GP or general practice nurse if it were available and how comfortable they would be discussing feeling afraid with the GP. It is explained in the screen survey that not every woman who provides her contact details can be contacted by the project team.

#### Trial phase

The primary outcomes (Table 1) include quality of life, measured across four dimensions (physical, psychological, environmental, social) using the WHOQoL-Bref [58], and mental health status, using the mental component of the SF-12 [59]. The third primary outcome is safety and is measured based on the existence of a safety plan (yes/no) and the number of safety behaviours enacted (Safety-Promoting Behaviour Checklist [60]). The secondary outcomes include open ended questions about readiness for change, based on the Domestic Violence Survivor Assessment [61], comfort to discuss abuse with GP (5-point likert scale), GPs' inquiry about the safety of women and their children (yes/no) and anxiety and depression, based on the Hospital Anxiety and Depression Scale [62]. Health care utilisation is measured based on visits to health professionals, days out-of-role and hospital admissions. Other variables measured at different stages of the trial were included to investigate mediating variables (see Table 2) and to provide process data to help understand why the intervention may or may not have been effective. Harm associated with participation in the research (e.g. acceptability of screening, distress caused by being invited into the project, partner's awareness of the research, adverse effects arising from participating in counselling, response burden) was measured using an adapted version of the COST questionnaire [31].

**Table 2 T2:** Other variables and measures included in 6 and 12 month surveys

Variable	Measure/tool
Sense of safety	How safe have you felt at home in the last two weeks/6/12 months ago? (visual analogue scale)
Safety behaviours	What things do you do (or have you done in the last 6 months) to keep you safe from your partner or ex-partner? (open-ended question)
Nature/frequency of abuse	Composite Abuse Scale [7]
Health status	Short Form-12 (PCS) [59] Smoking Alcohol (AUDIT) [69] Medications (analgesics, antidepressants and sedatives)
Post-traumatic stress disorder	Short Screening Scale for DSM-IV PTSD [70]
Self-esteem and self-efficacy	Rosenberg Self-Esteem Scale [71] Generalized Self-Efficacy Scale [72]
Social support	Oslo 3 Social Support [73]

The readiness of GPs to manage intimate partner abuse is assessed before and after the training using PREMIS, a validated questionnaire assessing knowledge, attitude and behaviours of doctors with regard to IPA [63].

#### Economic evaluation

The primary economic evaluation will use a cost-consequences analysis, with any incremental costs compared to all incremental outcomes as detailed above. If this does not reveal a dominant result for the cost-effectiveness of the intervention, secondary economic analysis will involve incremental cost-effectiveness analysis using individual outcome measures and cost-utility analysis using SF-12 data. The economic evaluation will be conducted from both a health care and societal perspective, with costs including resources used in intervention delivery and practice-based system change and women's use of health care and other societal resources.

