### Aims of weave

The primary aim of the **weave **study is to determine if a multifaceted intervention consisting of screening for intimate partner abuse and feedback for GPs, training for GPs, a brief counselling intervention for women and minimal practice organisational change results in:

• increased quality of life;

• increased mental health, and;

• increased safety behaviours and planning for women who experience partner abuse.

The secondary aims are to determine if the intervention results in:

• increased readiness for change with regard to the abuse;

• increased comfort on the part of women to discuss partner abuse with GPs;

• increased inquiry by GPs about the safety of women and children;

• reduced anxiety and depression;

and is cost effective.

We hypothesise that the brief counselling intervention will increase women's perceived support and comfort to discuss abuse and lead to positive changes in women's self-efficacy and readiness to change, and that these 'internal' changes will collectively lead to increases in safety planning and behaviours and improvement in mental health and quality of life.

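### The secondary cost-effectiveness and cost-utility analyses run only if no dominance is seen, so a chance cost estimate can leave a real trade-off unquantified

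*Protocol article*

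**What the plan says.** Under Aims of weave, the last of the secondary aims is to find out whether the intervention works "and is cost effective". The Economic evaluation section describes the primary analysis as a "cost-consequences analysis, with any incremental costs compared to all incremental outcomes as detailed above". It then states the condition: "If this does not reveal a dominant result for the cost-effectiveness of the intervention, secondary economic analysis will involve incremental cost-effectiveness analysis". The rest of that sentence names what these secondary analyses consist of: "using individual outcome measures and cost-utility analysis using SF-12 data". On scope it says: "The economic evaluation will be conducted from both a health care and societal perspective".

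The precision available follows from Number of participants required: "The final sample size of 89 women in each of the two groups will have at least 80% power", with "alpha 5%, 2-sided test" and an "intra-cluster correlation of 0.02", from 20 GPs in each arm.

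The Data analysis and reporting section describes no economic analysis that would run whatever the cost-consequences comparison shows.

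**The concern.** The condition is stated in the article. An analysis plan could say how dominance is judged, but it could not make the secondary analyses unconditional without departing from that sentence.

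Two features make the condition a poor one. First, what triggers it is not a single state. Costs are set against all outcomes from two perspectives, so the intervention may look dominant on one measure or perspective and not on another. The article does not say which reading stops the later analyses. Second, the sign of an estimated cost difference is uncertain at this sample size. An intervention that improves outcomes at a modest true extra cost can look cheaper by chance. The cost-effectiveness and cost-utility analyses would then not be required, although there is a real trade-off to be priced.

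**Working it through.** **Inputs from the article.** 89 women per arm at 12 months, 20 GPs per arm and ICC 0.02 (Number of participants required). Hypothesised differences of 0.5 SD for the continuous primary outcomes and 10% against 40% for having a safety plan (Table 1). Seven primary measures (Trial phase): four WHOQoL-Bref dimensions, the SF-12 mental component, safety plan and safety behaviours.

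**Assumptions not in the article.** Estimated differences are approximately normal. Costs have the same ICC as outcomes and are uncorrelated with effects. Pairwise correlation between outcomes is 0.3 to 0.7. Dominance is read from point estimates (cheaper and better).

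**1. The plan's own figure.** Mean cluster size is 89/20 = 4.45, so the design effect is 1 + (4.45 − 1) × 0.02 = 1.069. A 0.5 SD difference at 80% power and two-sided 5% needs 63 per arm without clustering, and 63 × 1.069 = 67.3 with it. At 89 per arm the power is 0.897 for 0.5 SD and 0.996 for 10% against 40%. The claim of at least 80% is reproduced. The article gives no figure for the economic rule.

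**2. Precision.** The standard error of a standardised difference is √(2 × 1.069 / 89) = 0.155 SD, and the 95% interval is about ±0.30 SD.

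**3. No true difference in cost or effect.**
- One outcome: 0.5 × 0.5 = 25%.
- All seven measures must agree, correlation 0.5: the chance that seven equally correlated estimates are all positive is 1/8, so 0.125 × 0.5 = 6%. Simulation with 400,000 draws gives 3% at correlation 0.3 and 10% at 0.7.

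**4. No true effect, true extra cost.** The chance that the cost estimate falls below zero is Φ(−0.1/0.155) = 0.26 for 0.1 SD and Φ(−0.2/0.155) = 0.10 for 0.2 SD.

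| True extra cost | Appears dominant, one outcome | Appears dominant, seven measures (correlation 0.5) |
|---|---|---|
| 0.1 SD | 13% | 3% |
| 0.2 SD | 5% | 1% |
| 0.5 SD | below 0.1% | below 0.1% |

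**5. True gain of 0.5 SD, true extra cost.** The effect estimate is almost always positive (Φ(0.5/0.155) > 0.999), so the reading turns on the sign of the cost estimate. The intervention appears dominant in about 26% of trials at 0.1 SD extra cost, 10% at 0.2 SD, 3% at 0.3 SD and below 0.1% at 0.5 SD. Requiring agreement on seven measures gives no protection if all seven truly improve by 0.5 SD: the simulated figure at 0.1 SD is again about 26%.

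**The case against.** The strongest reply is that the sequence is coherent. Under dominance there is no trade-off to price and a negative ratio is hard to interpret, so computing a ratio only when costs and effects point the same way is a reasonable order of work. How dominance is judged and how uncertainty is displayed are details that a condensed article may leave to a fuller plan. The choice of net-benefit or bootstrap methods is also a matter for that plan.

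Much of this stands, and it rules out several stronger readings that a reader might infer:

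- *That the main economic analysis depends on the data.* It does not. The cost-consequences analysis is the primary one and always runs; only the secondary analyses are conditional.
- *That dominance will be read from point estimates and reported without uncertainty.* The article says neither. It gives no criterion, and silence on that detail is not itself a fault. The point-estimate reading is an assumption here.
- *That 25% is the error rate of the stated rule, or that it rises with more outcomes.* It applies to one outcome with no cost difference. If all outcomes must agree, the null figure falls to about 6%, and a mixed result would not be dominance, so the secondary analyses would run. The chance rises with more outcomes only if dominance on any one of them is enough.
- *That the condition stops the analyses half the time.* That would also count trials in which the intervention looks worse and dearer. The wording does not clearly say that such a result stops the later analyses.

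Zero extra cost is also a favourable case for the concern. Only the intervention arm receives the practice visits and the counselling of up to six sessions, and delivery costs are counted, although lower use of services elsewhere could offset them.

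The reply does not remove the condition itself. When there is a modest real extra cost, apparent dominance is the very case in which the trade-off needs to be quantified.

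**Conclusion.** The point holds as a minor one. The article fixes a rule under which the only analyses giving a cost per unit of benefit or per utility gain depend on the observed cost-consequences result. That comparison spans at least seven measures and two perspectives, with a standard error of about 0.155 SD.

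Under the stated assumptions, chance dominance with no true difference ranges from about 6% (all seven measures agreeing; 3% to 10% over the correlations tried) to 25% (one outcome). It is lower if the intervention truly costs more. The more practical case is a successful intervention with a small extra cost of 0.1 SD: about 26% of trials would show dominance on one outcome and leave the trade-off unquantified. The risk is negligible once the true extra cost is near 0.5 SD. The article gives no expected cost difference, so where this trial lies in that range is unknown.

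The issue touches a secondary aim. It does not affect the primary clinical outcomes, the sample size or the primary economic analysis.

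**What to change.** Delete the condition. Run the SF-12 cost-utility analysis and the incremental cost-effectiveness analyses whatever the cost-consequences comparison shows, from both the health care and the societal perspective. Report joint uncertainty in costs and effects with a method that keeps the GP clusters and the correlation between cost and effect, for example a two-stage cluster bootstrap or a bivariate mixed model. Keep the cost-consequences table as the primary, descriptive analysis. Report the probability of dominance as a result instead of using dominance as a gate.

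The change needs no extra data and no change in sample size. It costs modest additional analysis work.
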